**Figure 3 fig3:**
[figure not shown]
Flow diagram of study participants.

### Ethics statement

3.6

This study was carried out in accordance with the recommendations of the National University of Singapore (NUS) with written informed consent from all subjects. All subjects gave written informed consent in accordance with the NUS Human Biomedical Research guidelines.

### Progress and next step

3.7

We have made significant progress in laying the foundation for our proposed studies. The DaHA study has successfully completed two waves of data collection. Wave 1 (2011–2017) recruited 1,010 community-living older adults aged 60 years and above in Singapore, collecting comprehensive data on lifestyle factors and cognitive function. Wave 2 (2017–2020) followed up with over 600 survivors (aged 62–91), providing valuable longitudinal data through established cognitive assessments. This rich dataset forms the basis for the planned 10-year cognitive assessment follow-up, which aims to further explore the longitudinal relationships between diet, nutrition, and cognitive health.

As for the next step, first, we will formally recommend that the Ministry of Health Singapore include mushroom consumption as a primary preventative measure in its Clinical Practice Guideline for Dementia. We will recommend that the Health Promotion Board Singapore include moderate mushroom consumption as a component in their public education and health communication programs that aim to promote healthy and functional aging. We will publish our findings in leading journals, present them at key international and local conferences, and share them with practitioners in Singapore and beyond. As a result, we anticipate that clinicians will recommend regular mushroom consumption to older adults consulting specialists or general practitioners for memory concerns. This recommendation will also extend to individuals at high risk of dementia due to family history or genetic testing, aiming for favorable clinical outcomes. Second, we will conduct further research to confirm long-term efficacy among RCT participants. We plan to conduct extended follow-up assessments 5 years post-baseline to assess clinical progression (defined as an increase in CDR global score from 0 to 0.5 or higher) and to identify incident cases of dementia in both the intervention and control groups. This extended follow-up study will be completed 3 years after the completion of the currently proposed study and will provide further evidence to strengthen the conclusions from the proposed trial. Last, the research team will seek potential public or private funding sources to form a spinoff/startup company focusing on the development of novel plant-based medical foods and nutraceutical products. The applicant and coworkers have been working on the cognitive benefits of various plant-based compounds. With a strong scientific foundation and a successful track record, we believe that establishing a spinoff/startup company specializing in phytoceuticals, nutraceuticals, and medical foods is highly feasible. This feasibility is supported by Singapore’s favorable biomedical R&D environment and potential funding from governmental bodies, venture capitalists, angel investors, and modern funding methods such as crowdfunding. The potential benefits for Singapore’s healthcare sector and economy are substantial and expansive.

## Discussion

4

Mushroom consumption is safe and is likely to be embraced by older adults in the community as a preventive intervention. Although compliance to the intervention may raise as a potential problem given the long study period of two years, we have proposed the following methods to address this potential difficulty and limitation: (1) study staff to give weekly phone calls to remind study participants of the regime they are supposed to follow; (2) compliance will be monitored via a simplified one-touch electronic diary app (large icons, single-button “check-in”), augmented by automated push/SMS/phone reminders, caregiver assistance for entry, and cross-validation using electronic pill caps. Compliance rate can be used as a covariate in statistical analysis. Per-protocol analysis will be conducted on a subsample of subjects who have a compliance rate of 85% or above. Although we include a placebo control and blinding, repeated cognitive testing may introduce practice effects. We will account for this by including the assessment session (visit number) as a covariate in our longitudinal models, and where validated alternate forms exist, we will use them. With positive results and strong evidence, mushroom consumption and supplementation could be recommended as an important and simple method for promoting cognitive health in aging individuals and as a public health measure at the population level. This will potentially lead to healthcare cost savings. Furthermore, this study could provide evidence for the development of new nutraceutical products, with further translational research. The proposed study will provide more definitive data on the efficacy of mushrooms in preventing cognitive decline among individuals who are at high risk of dementia. Translating these findings into clinical and public health practice could lead to improved cognitive health and a reduced incidence of dementia. This, in turn, could result in substantial savings on the direct and indirect cost of dementia care in Singapore. The research will also provide insights into the biological mechanisms underlying the putative effect of mushroom powder on cognitive decline. By addressing scientific questions not previously rigorously examined, this research can strengthen our conclusions regarding clinical efficacy.

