#### Standardization

3.3.1

Participants randomized to the mushroom powder intervention arm will be instructed to consume daily for 24 months. Electronic diary apps will be used to monitor compliance. The Pleurotus citrinopileatus extract will be supplied by Guangdong Yuewei Edible Fungi Technology Co., Ltd. (Guangzhou, China). Dried fruiting bodies (1 kg) were mixed with distilled water (25 L), then boiled under reflux for 2 h. The slurry was filtered and centrifuged (4,000 rpm, 15 min) to yield the extract, which was vacuum-concentrated to 1/10 volume, blended with 20% maltodextrin, and spray-dried at high temperature. Final powder contained 1.0% ergothioneine (HPLC-UV quantification). We selected a daily ergothioneine dose of 10 mg (two 500 mg capsules of Pleurotus citrinopileatus extract at 1% ET), corresponding to 70 mg ET per week. This falls within the range of prior human interventional studies: Yau et al. administered 25 mg ergothioneine per capsule, three times per week (75 mg ET/week) for one year (Yau et al., 2024); Mori et al. gave four 250 mg tablets of Hericium erinaceus dry powder (96% purity, ~960 mg powder per dose) three times daily (~2.88 g powder/day) for 16 weeks—both regimens were well tolerated (Mori et al., 2009). Participants in the control arm will consume placebo capsules. Participants and assessors will be blinded to the randomization. The mushroom powder will be derived from the mushroom species *Pleurotus citrinopileatus*. The dried fruiting bodies of *Pleurotus citrinopileatus* have an ergothioneine content of 10.0 mg/g (dry weight). The following figure is a diagram of the *Pleurotus citrinopileatus* body and its preparation method (Figure 2).

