### Methods of analysis

3.5

To test the relationship between mushroom consumption and cognition among cohort participants: A linear regression model will be used to assess how baseline mushroom consumption predicts future cognitive changes. A log-binomial regression model will be used to compare the proportion of incidental cognitive impairment cases in the subgroups defined by mushroom consumption. A sensitivity analysis will be performed using a log-binomial model for repeated measures, including assessments at the 5-year follow-up and controlling for major demographic, medical, and lifestyle factors. Pre-specified subgroup analyses will stratify by baseline cognitive status (MMSE ≥ 27 vs. < 27), sex, and education level (≤ secondary vs. > secondary). Interaction terms will test for differential intervention effects.

*A priori* power calculation was performed using G*Power 3.1. Assuming a small-to-medium effect size of Cohen’s d = 0.30 in 24-month MMSE change, two-tailed *α* = 0.05 and 90% power, 235 subjects per arm are required. Allowing 20% attrition at 24 months (Jacobsen et al., 2021), we plan to enroll 300 per arm.

To test the effects of ET-Rich mushroom powder on cognitive function among RCT participants: A linear regression model will be performed to compare changes in cognitive scores at 24 months between the intervention and control arms. A sensitivity analysis will be performed using a general regression model for repeated measures, including assessments at 12 months and controlling for major demographic, medical and lifestyle factors at baseline.

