To examine the underlying protective mechanisms: The levels of biomarkers will be treated as continuous variables. Changes in biomarkers will be calculated by comparing post-intervention levels to pre-intervention levels from intervention and control and represented in percentage (%). These changes will then be compared between the intervention and control groups. Furthermore, paired two-tailed t-tests will be performed to assess whether biomarker levels differ between pre-intervention and post-intervention measurements within each group (control and intervention). To analyze the ergothioneine data, we will use a “change-versus-change’ approach, using repeated ergothioneine measurements as predictors to examine their relationship with changes in cognition and other biomarkers. We will further employ Structural Equation Modeling (SEM) to assess how the intervention affects cognitive function, with ergothioneine as a hypothesized mediating factor. In the SEM, we will adjust for age, sex, education (social class proxy), BMI, APOE ε4 status, baseline supplement use (curcumin, Ginkgo, omega-3), individual metabolic variations by including plasma liver enzymes (ALT, AST) and baseline renal function & ergothioneine levels as covariates, and compliance rate. Interaction terms will test effect modification.

To examine the epigenetic changes associated with ET-Rich mushroom consumption: Analysis of epigenome-wide methylation data will be performed using a modified version of the CPACOR pipeline(Lehne et al., 2015). Briefly, we will normalize marker intensities by quantile normalization. Single-marker tests using logistic regression will be used to examine the association of mushroom consumption with each autosomal CpG site (yes/no), adjusted for age and sex. Principal components from intensity values of Infinium control probes will also be included as covariates in the regression models. Finally, the association results will be adjusted for the genomic control inflation factor. We will subsequently develop a methylation risk score (MRS) model by taking a weighted approach (by effect size) for the CpG loci identified to be associated with mushroom consumption. Figure 3 describes the flow of study participants.

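### The mediation model is to adjust for compliance, a post-randomisation variable, and the Discussion leaves compliance open as a covariate in any analysis

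*Protocol article*

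**What the plan says.** Two places in the protocol article bring compliance in as a covariate.

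- **Methods of analysis (3.5).** An SEM is to assess how the intervention affects cognition, "with ergothioneine as a hypothesized mediating factor". The variables it will adjust for are otherwise participant characteristics and baseline or laboratory measures, and the list ends "baseline renal function & ergothioneine levels as covariates, and compliance rate". This is a firm commitment.
- **Discussion (4).** In the paragraph on managing poor adherence: "Compliance rate can be used as a covariate in statistical analysis". This is a permission. It names no model and excludes none.

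The timing is clear. Under Standardization (3.3.1), "Participants randomized to the mushroom powder intervention arm will be instructed to consume daily for 24 months", and the Discussion says "compliance will be monitored via a simplified one-touch electronic diary app", cross-checked with electronic pill caps. Compliance is therefore observed only after assignment.

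The specified cognitive comparisons in section 3.5 do not include it. The main analysis reads "A linear regression model will be performed to compare changes in cognitive scores at 24 months between the intervention and control arms", with no compliance term. The repeated-measures sensitivity analysis is described as "controlling for major demographic, medical and lifestyle factors at baseline". The Discussion also plans a separate per-protocol analysis in participants with compliance of at least 85%.

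**The concern.** Randomisation balances what exists before assignment. Compliance comes afterwards. It can respond to the assigned product, for example through tolerability, and it can respond to the participant's own cognitive course, because someone who is declining may forget capsules and diary entries. In a population selected for dementia risk, with cognition as the outcome, a link between compliance and outcome is plausible. If compliance also differs between arms, comparing arms at equal compliance compares people who differ in other ways, and the contrast is no longer the randomised one.

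The SEM has a further difficulty. On the active arm, capsule-taking lies between assignment and blood ergothioneine. If poor cognition also lowers capsule-taking, compliance is at the same time a confounder of the ergothioneine–cognition link. An ordinary covariate term cannot serve both roles. At stake is the mechanistic aim (aim 3 in section 2): the reported direct, indirect and total effects may not be the ones intended. The open permission in the Discussion would let the same problem into any arm comparison.

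**Working it through.** **1. The plan's own figure.** Inputs from section 3.5: d = 0.30 on 24-month MMSE change, two-sided alpha 0.05, power 90%, attrition 20%. The normal approximation gives 2 × (1.960 + 1.282)² / 0.30² = 233.5, so 234 per arm; the t-test solution is 234.46, so 235, as stated. Then 235 / 0.80 = 293.75, so 294, within the planned 300. None of this depends on compliance.

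**2. Bias in an adjusted arm effect.** In a linear model, adjusted effect = unadjusted effect − (within-arm slope of outcome on compliance) × (active minus control difference in compliance). In SD units the shift has size r × delta. The article gives neither quantity, so both are assumed:

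- delta = 0: shift 0, whatever r is.
- r = 0.1, delta = 0.1: 0.01 SD, and 0.01 / 0.30 = 3% of the design effect.
- r = 0.5, delta = 0.4: 0.20 SD, and 0.20 / 0.30 = 67%.

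If better compliers do better, the shift favours the arm with lower compliance.

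**3. Simulation check of the formula** (400,000 participants, assumed inputs). A prognostic factor drives compliance at 0.5 and outcome at 0.4, so r = 0.5 × 0.4 = 0.20. Compliance is lower on active by 0, 0.3 or 0.6 SD; the formula predicts shifts of 0, 0.06 and 0.12.

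- No true effect: unadjusted about 0.00 throughout; adjusted 0.00, 0.05, 0.11.
- True effect 0.30: unadjusted 0.30 throughout; adjusted 0.30, 0.36, 0.42.

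**4. The mediation model.** Compliance is generated as in step 3. Ergothioneine = arm × (1 + 0.4 × compliance) + noise; cognition = 0.3 × ergothioneine + 0.4 × prognostic factor + noise, with noise SD 1. The whole effect runs through ergothioneine, so the true direct effect is 0 and the true ergothioneine-to-cognition path is 0.30. Each cell from the second column on shows the estimate without / with compliance in the model.

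| Gap (SD) | Total | Arm to ergothioneine | Ergothioneine to cognition | Indirect (true value) | Direct |
|---|---|---|---|---|---|
| 0 | 0.30 / 0.30 | 1.00 / 1.00 | 0.34 / 0.30 | 0.34 / 0.30 (0.30) | −0.04 / 0.00 |
| −0.3 | 0.27 / 0.35 | 0.88 / 0.94 | 0.34 / 0.30 | 0.30 / 0.28 (0.26) | −0.03 / 0.06 |
| −0.6 | 0.23 / 0.38 | 0.77 / 0.88 | 0.33 / 0.30 | 0.26 / 0.26 (0.23) | −0.03 / 0.12 |

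Reading across:

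- With compliance in the model, the ergothioneine-to-cognition path is right. Once there is an arm gap, however, the total effect is inflated and a false direct effect appears.
- Without compliance, the total effect is right, but the ergothioneine-to-cognition path is too large even with no gap.
- With an arm gap, the indirect effect is wrong both ways.
- The arm-to-ergothioneine path does not vanish under adjustment; here it rises.

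**The case against.** The strongest case on the other side has four parts.

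- **The primary analysis is not affected as specified.** A reader might infer from the Discussion sentence that the main cognitive comparison will be adjusted for compliance. The documents do not support that: section 3.5 gives the main regression no compliance term and ties the sensitivity analysis to baseline factors. This stands. The commitment is firm only for the SEM, which is a mechanistic analysis.
- **Adjustment does not wipe out the ergothioneine signal.** A reader might infer that holding compliance fixed removes the variation in ergothioneine produced by the intervention. It does not. The control arm takes placebo capsules, understood here to contain no ergothioneine, so at equal compliance the arms still differ in exposure. This also stands, and the table agrees.
- **Deleting compliance from the SEM is not a cure.** If decliners forget capsules, compliance confounds ergothioneine and cognition, and dropping it leaves that path biased (0.33 to 0.34 against 0.30 in the illustration). This stands and determines the fix.
- **The arm gap may be negligible.** Participants and assessors are blinded and control is by placebo. With no gap the arm effect is not biased. This stands as a limit on size. It does not justify the covariate, because the gap cannot be known in advance.

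The planned 85% per-protocol analysis does not answer the point, since selecting on compliance is also conditioning on a post-randomisation variable.

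**Conclusion.** The point holds in a limited form. The SEM is committed to adjusting for a post-randomisation variable, and the Discussion leaves that variable available to every other analysis. Where compliance differs by arm and shares causes with cognition, the adjusted arm effect, total and direct, moves by about r × delta: nothing without an arm gap, and 0.01 to 0.20 SD over the assumed range, against the planned 0.30. For the indirect effect, neither keeping compliance as an ordinary covariate nor dropping it is generally adequate.

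All sizes rest on assumed correlations and gaps, because the article reports no expected compliance by arm. The direction of the shift depends on which arm complies less. The comparison with 0.30 is a yardstick for what the open permission could do; it is not evidence that the specified primary analysis is biased. The plan should be changed before data are seen, but the trial's design does not hinge on it.

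**What to change.** 1. **Discussion (4).** Replace the sentence on compliance as a covariate with: *arm comparisons adjust for baseline covariates only; compliance is not a covariate*.
2. **Methods of analysis (3.5), SEM.** Estimate the total and arm effects without compliance. For the ergothioneine pathway, use a mediation method that allows a mediator–outcome confounder arising after randomisation, for example interventional indirect effects or g-estimation. Show results with and without compliance as a sensitivity check.
3. **Per-protocol analysis.** Label the 85% compliance subset supportive. A complier-average estimate with assigned arm as instrument is an optional supplement for the effect among those who take the capsules.

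The cost is wording and a modest amount of extra analysis, with a wider interval for the indirect effect. The sample size stays at 235 evaluable and 300 enrolled per arm.
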